## Abstract

The aim of the study is to analyze the effect of smoking and smoking cessation on the incidence of complications among orthopedic and hand surgery patients, and to determine the feasibility of smoking cessation intervention, as well as factors predicting success in smoking cessation. Orthopedic and hand surgery patients will be invited to participate in the study, which will recruit 550 participants (at least 20% daily smokers). A participant will be defined as a daily smoker if he/she reports daily smoking and/or laboratory tests show active smoking. Data will be collected using a self-reported questionnaire and from medical records. Smokers will receive information about the benefits of smoking cessation and will be encouraged to quit. Medication or nicotine replacement therapy will be prescribed. Laboratory tests will be taken two weeks before and two weeks after surgery. Follow-up phone calls will be made at 3, 6, and 12 months after surgery. The primary outcome is any complication, defined as a prolonged stay in hospital or any additional visit to or measure taken by a health service during the 12 months after surgery. Data on complications are mainly obtained from personal health records and from the information received at the follow-up; the rest of the data will be collected from the register of healthcare-associated infections. Secondary outcomes are the number and types of complications. The sample (n=550) was calculated to observe a 10% difference in complications between smokers and non-smokers (5% alpha level and 80% power), considering a 10% drop-out rate. Logistic regression and log-linear models will be used for data analyses.

## INTRODUCTION

Smoking has many adverse effects on orthopedic and hand surgery patients. It impairs blood circulation in the area of surgical intervention^1,2^, oxygenation of tissues^3,4^, and immune response to infections^5,6^. Smoking increases the risk of thrombosis in vessels^7,8^. Further, it impairs the function of osteoblasts^9^, decreases the resorption of calcium from the intestines^10^, and lowers the level of vitamin D^5^.

Smoking also hinders wound healing^11^. Tibial, femoral, humeral, clavicular, and wrist navicular fractures heal more slowly in smokers than in non-smokers^12-17^. The healing of ankle arthrodesis^18^, high tibial osteotomy^19^, and ulnar shortening osteotomy^20^, is also slower and more uncertain among smokers than among non-smokers. Smokers have more complications on hip and knee arthroplasties compared with non-smokers^21,22^. The outcome of spinal surgery is worse for smokers than for non-smokers^23,24^. Smokers have six-fold overall risk of surgical wound infections compared with that of non-smokers^25^.

Nåsell et al.^26^ have shown that in the smoking cessation intervention group, 20% compared with 38% in the control group had surgical complications after acute fracture surgery. In another study by Møller et al.^27^, the overall complication rate was 18% in the smoking cessation intervention group and 52% in the control group, and the median length of hospital stay was 11 and 13 days, respectively. Glassman et al.^28^ have shown that smoking cessation for longer than six months after a posterior instrumented lumbar spinal fusion reduces the rate of nonunion to 17% compared with 26% for those who continued to smoke after surgery. The nonunion rate was 14% among non-smokers. In a study of elective orthopedic and special surgery patients with a smoking cessation intervention of four weeks before and four weeks after surgery, the incidence of postoperative complications was 21% in the intervention group and 41% in the control group^29^.

Hejblum et al.^30^ have shown in their cost-benefit analysis that a smoking cessation intervention of hip and knee arthroplasty patients saved on average 117 € per patient in 2008. The average 90-day cost of total joint arthroplasty with a smoking cessation intervention was 32 US$ less than the respective cost without intervention in 2017^31^. In the US, the mean cost of a total hip arthroplasty with a periprosthetic infection was over 88 thousand US$ and that without a periprosthetic infection over 25 thousand US$, from 2007 to 2011^32^. So, the mean cost of a periprosthetic infection after a total hip arthroplasty was close to 63 thousand US$ . In all, smoking cessation preoperatively is a very valuable and cost-effective method of reducing the risks of postoperative complications, especially infections of orthopedic patients. With this intervention, a significant amount of money could be saved. Further, smoking cessation is a very effective method to improve health^33^. Tosi et al.^34^ have reported that an intervention program among patients who had a low-energy fracture and who received counselling on calcium and vitamin-D supplementation, weight-bearing exercise, smoking cessation, and fall prevention, reduced the risk of secondary fractures.

It is very challenging to motivate smokers to quit before orthopedic or hand surgery. This is even though we know very well that the risk of complications is much lower when a patient stops smoking before surgery. Lindström et al.^29^ found that a significant proportion of their patients were not interested in smoking cessation and they wanted only to concentrate on the forthcoming surgery. Bender et al.^35^ showed, in their study of patients who had surgery for long bone nonunion, that only 8% of smokers had stopped smoking at six weeks after surgery.

### Aims

This article describes the protocol of our study which aims to determine: 1) the effects of smoking and smoking cessation intervention on the incidence of complications after orthopedic surgery; 2) the feasibility of preoperative smoking cessation intervention and its effect on reducing smoking; and 3) which factors predict success in smoking cessation. The secondary aims of the study are: a) to compare the incidence of different types of complications in the whole study population and in different subgroups of orthopedic and hand surgery patients who are smokers, non-smokers or quitters who stopped smoking during the preoperative intervention; and b) to determine which other factors in addition to smoking, such as chronic diseases and medication, explain the incidence of complications.

### Hypotheses

Smoking patients have more complications compared with non-smoking patients and patients continuing smoking despite smoking cessation intervention have more complications than initially smoking patients who are stopping smoking because of the intervention.Smoking cessation of patients with planned arthroplasties or heavy spine operations or other heavy operations, and of patients with low or moderate nicotine dependence, is successful more often than in other patients.

## METHODS

### Recruitment

Participants for the study will be recruited among patients visiting the orthopedic or hand surgery outpatient department and who are on the waiting list for elective orthopedic or hand surgery in Päijät-Häme Central Hospital, Lahti, Finland (Figure 1). The orthopedic surgeon (who registers the patient on a waiting list) and nurse decide if the patient is eligible to participate in the study.

**Figure 1 f0001:**
[figure not shown]
Sequence of procedures

The eligibility criteria are at least 18 years of age and that the planned surgery will be directed at the bone. Patients under 18 years of age, patients with an acute fracture, and patients awaiting other types of surgery are excluded from the study. A total of 550 patients will be recruited aiming to have at least 20% of them daily smokers, corresponding approximately to the current smoking prevalence in Finland^36^. The number of smokers will be followed up during the process so that more could be recruited during the recruitment period if their proportion seems too small.

### Data collection

Participants fill in a self-reported questionnaire collecting detailed background information on chronic diseases, medication, socio-economic status, physical activity, and use of alcohol. The questionnaire includes questions on present and past smoking; use of electronic cigarettes, snus, and pipe tobacco; and exposure to passive smoking. Additional and clarifying information such as diagnoses of chronic diseases and prescribed medication will be collected from participants’ personal health records. Information on the orthopedic diagnosis and planned orthopedic surgery will be filled in on the study form (Figure 1).

During the preoperative assessment at about two weeks before the surgery, laboratory tests will be taken to verify the smoking status of the participants and to differentiate the use of other nicotine products (by cotinine of urine, U-Cot and carboxyhaemoglobin, Hb-CO) and to exclude malnutrition (albumin of serum, S-Alb) and other significant catabolic processes (C-reactive protein, P-CRP) (Figure 1). Participants’ smoking history will be based on classification used in surveys conducted by the Finnish National Institute for Health and Welfare (THL) and categorized from 1 to 5 as follows: 1=daily smoker, 2=occasional smoker, 3=quit smoking 1–12 months ago, 4=quit smoking over 12 months ago, and 5=never smoker^36^.

During the intervention, participants’ smoking status will be confirmed using the following criteria. A participant is determined as a smoker if he/she reports daily smoking and/or U-Cot is above 250 µg/L and Hb-CO above 2%. A participant who reports exposure to passive smoking and/or has a U-Cot of 100–250 µg/L, is categorized as a passive smoker. Among non-smokers, U-Cot is typically <50 µg/L and Hb-CO <2%. Hb-CO is used to specify users of snus or NRT, among whom Hb-CO is <2% but U-Cot is elevated.

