### Intervention

Smokers will be given verbal and written information about health and economic benefits of smoking cessation and encouraged to quit smoking. The Fagerström test for nicotine dependence (FTND) will be conducted to estimate the level of nicotine dependence of smokers^37^. If a smoker has moderate nicotine addiction, NRT will be recommended. Prescription medication to aid smoking cessation will be considered if a participant had strong nicotine dependence, i.e. smoked over 10 cigarettes per day and first cigarette was lit within 30 minutes after waking up, or a previous attempt to quit smoking yielded significant withdrawal symptoms^38^.

The smoking cessation intervention will be given in the outpatient department, by the surgeon, the nurses, or both. In discussions with smokers, the aim is to share information, persuade, motivate, and offer skills training and social support to quit smoking. The intervention will be performed during an outpatient appointment when the patient is registered on the waiting list and also during the preoperative visit. After surgery, when the stitches will be removed, Hb-CO and U-Cot tests will be repeated to verify participants’ smoking status to verify successful smoking cessation. Participants will be followed up to 12 months after surgery. Participants will receive a phone call or letter at 3, 6, and 12 months after surgery, asking them if any problems or complications had occurred (Figure 1). The description and ICD codes of complications will be recorded in the study form.

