### Primary and secondary outcomes

The primary outcome is any complication occurring within 12 months after surgery. The number and types of complications (for example rapidly occurring complications, repeat surgery, and infections, stratified by types of surgery) are considered as secondary outcomes. Subgroup analysis based on patient characteristics and comorbidities will be carried out. Successful smoking cessation is a feasibility outcome.

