### Data analyses

To analyze the risk of primary outcome, i.e. the postoperative complications among smokers, non-smokers, and quitters, a logistic regression model will be used. The effectiveness of the smoking cessation intervention will be assessed using logistic regression analyses. Associations of smoking status and background variables with complications will be analyzed using log-linear models considering patients’ gender, age, and comorbidities.

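### High urine cotinine with low Hb-CO is never classed as smoking unless the participant admits daily smoking, and no nicotine product use need be documented to explain it

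*Protocol article*

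**What the plan says.** Under Data collection, the protocol article gives one rule for an active smoker: "A participant is determined as a smoker if he/she reports daily smoking and/or U-Cot is above 250 µg/L and Hb-CO above 2" (per cent). Two further sentences there deal with other results:

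- "A participant who reports exposure to passive smoking and/or has a U-Cot of 100–250 µg/L, is categorized as a passive smoker". This band stops at 250 µg/L, so it does not cover the results discussed here.
- "Hb-CO is used to specify users of snus or NRT, among whom Hb-CO is <2% but U-Cot is elevated".

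The same section says that the questionnaire asks about snus and electronic cigarettes, and that prescribed medication is taken from health records. It does not say that this information enters the classification.

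Under Intervention, at stitch removal, "Hb-CO and U-Cot tests will be repeated to verify participants’ smoking status to verify successful smoking cessation". No other criterion for a quitter is stated.

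Smoking status is then used twice. Under Primary and secondary outcomes, "Successful smoking cessation is a feasibility outcome". Under Data analyses, the primary outcome is modelled by status: "the postoperative complications among smokers, non-smokers, and quitters, a logistic regression model will be used".

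The Discussion explains why the tests are done. In an earlier cohort, 23% of self-reported former smokers and 6% of self-reported non-smokers had serum cotinine suggesting active smoking. The authors expect some self-reported non-smokers here to be reclassified in the same way.

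**The concern.** The two markers look back over different periods. Carbon monoxide clears within hours and cotinine over days. Requiring both lets the short-window marker overrule the long-window one. A participant who still smokes, denies it, uses no nicotine product and has not smoked for some hours before a booked appointment would have high cotinine and low Hb-CO. The stated rule does not class that person as a smoker, and the only reading offered for the result is product use.

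These are people the Discussion says the tests should find. If they are missed at stitch removal, continuing smokers are counted among the quitters. If they are missed at the preoperative test, they are counted among the non-smokers. The first raises the feasibility outcome, and both blur the groups compared in the primary model.

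**Working it through.** **Step 1: the rule as a table.** The sentence can be parsed in two ways: (A) reports daily smoking, or (U-Cot > 250 and Hb-CO > 2%); (B) (reports daily smoking or U-Cot > 250), and Hb-CO > 2%. The Abstract's definition (self-report and/or laboratory tests) favours A. For a participant who does **not** report daily smoking:

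| U-Cot (µg/L) | Hb-CO | Smoker under A | Smoker under B |
|---|---|---|---|
| up to 250 | below or above 2% | no | no |
| > 250 | < 2% | **no** | **no** |
| > 250 | > 2% | yes | yes |

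The row in bold does not depend on the parse. However high the cotinine, it does not make a denier a smoker without Hb-CO above 2%.

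**Step 2: can a smoker fall in that row?** The documents give no clearance times, so these inputs are assumptions: Hb-CO half-life 3–6 h, background 0.5–1%, starting value 4–6%; cotinine half-life 16–20 h, starting U-Cot 500–2000 µg/L.

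- Hours until Hb-CO < 2% = half-life × log2[(start − background)/(2 − background)]. Shortest: 3 × log2(3.5/1.5) = 3.7 h. Longest: 6 × log2(5/1) = 13.9 h.
- Hours until U-Cot < 250 = half-life × log2(start/250). Shortest: 16 × log2(2) = 16 h. Longest: 20 × log2(8) = 60 h.

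On these assumptions, roughly half a day without smoking or less clears Hb-CO while U-Cot is still above 250 µg/L.

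**Step 3: quit rate.** The plan gives no figure for this error. Let q be the true quit rate, d the share of continuing smokers who deny smoking, and m the share of those whom Hb-CO misses. If those missed count as quitters:

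observed rate = q + (1 − q) × d × m

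| q | d | m | Observed |
|---|---|---|---|
| 0.30 (assumed) | 0.10 | 0.30 | 0.30 + 0.70 × 0.03 = 0.321 |
| 0.30 | 0.20 | 0.50 | 0.30 + 0.70 × 0.10 = 0.370 |
| 0.30 | 0.30 | 0.70 | 0.30 + 0.70 × 0.21 = 0.447 |
| 0.50 (the plan's upper assumption) | 0.20 | 0.50 | 0.50 + 0.50 × 0.10 = 0.550 |

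**Step 4: complication contrast (illustration).** From the sample size section: 550 × 20% = 110 smokers, less 10% drop-out = 99. If half quit, there are 49.5 quitters and 49.5 continuing smokers. Assume true complication rates of 30% in continuing smokers and 20% in quitters. A share f = d × m of continuing smokers passes as quitters, unrelated to their risk. The observed difference is then 10/(1 + f) points. Power is for a two-sided 5% comparison of two proportions by the normal approximation.

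| f | Apparent quit rate | Observed difference | Power |
|---|---|---|---|
| 0 | 50% | 10.0 points | 21% |
| 6% | 53% | 9.4 points | 19% |
| 10% | 55% | 9.1 points | 18% |
| 23% | 61.5% | 8.1 points | 15% |
| 30% | 65% | 7.7 points | 14% |

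The documents give no value for f. The 6% and 23% rows borrow the misreporting rates cited in the Discussion as a scale only; those rates come from serum cotinine in another population.

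**The case against.** The Hb-CO condition is deliberate. The intervention itself supplies NRT, so cotinine alone would label true quitters on NRT as smokers. **This stands**, and the condition should stay for documented users.

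The snus/NRT sentence describes product users and does not say that everyone with that pattern is classed as one. The full protocol may combine the laboratory values with the questionnaire. **This stands in part.** The product-user label and the quitter status are both inferred. What is stated outright is that the pattern is not smoking unless daily smoking is reported, and nothing in the text prevents the consequence.

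A reader might infer that the plan contradicts its own Discussion. It does not. The Discussion expects only that some deniers will be reclassified, and the rule does that when both markers are raised. It falls short of the purpose without contradicting it.

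A reader might also infer a bias in favour of the hypothesis that cessation by "patients with low or moderate nicotine dependence, is successful more often than in other patients", because "If a smoker has moderate nicotine addiction, NRT will be recommended". The documents do not support this. The present rule overlooks high cotinine with low Hb-CO at every dependence level, whether or not NRT is used. The hypothesis pools low with moderate dependence, and the Abstract does not tie NRT to any dependence level.

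Finally, participants who admit daily smoking are caught by self-report under the natural reading. The gap concerns only deniers and those who report less than daily smoking, and their number is unknown.

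**Conclusion.** The point holds as a cheap improvement. As written, cotinine alone never identifies a smoker who denies smoking, and documented product use is not required before high cotinine with low Hb-CO is taken as something other than smoking. Because the same tests verify cessation, such participants can pass as quitters or non-smokers.

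The direction for the quit rate is clear: among continuing smokers this cell can only add false quitters. Dilution of the complication contrasts follows only if the error is unrelated to complication risk. The size is not known. The range of 32–45% for a true 30% rests entirely on assumed denial and miss rates, and with the plan's own 50% the central case gives 55%. In the illustration, the loss in the quitter contrast is modest next to its already low power of about 21%.

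**What to change.** - **Rule.** Treat U-Cot above 250 µg/L with Hb-CO below 2% as snus or NRT use only when current use of a nicotine product is documented at that test, by questionnaire, health record or study form. Otherwise classify the participant as a smoker. The article does not say that product use is recorded at stitch removal, so one added question may be needed there.
- **Sensitivity analysis.** Repeat the quit rate and the complication contrasts with every participant above 250 µg/L, including documented NRT users, counted as not a verified quitter. This is needed because the revised rule still misses a denier who has documented NRT, and because it verifies documented users by Hb-CO alone while judging others on cotinine.

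**Cost.** One clause, possibly one question, and one analysis of data already being collected. A few undisclosed snus or e-cigarette users will be counted as smokers, and the reported quit rate may be slightly lower.

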### Intervention

Smokers will be given verbal and written information about health and economic benefits of smoking cessation and encouraged to quit smoking. The Fagerström test for nicotine dependence (FTND) will be conducted to estimate the level of nicotine dependence of smokers^37^. If a smoker has moderate nicotine addiction, NRT will be recommended. Prescription medication to aid smoking cessation will be considered if a participant had strong nicotine dependence, i.e. smoked over 10 cigarettes per day and first cigarette was lit within 30 minutes after waking up, or a previous attempt to quit smoking yielded significant withdrawal symptoms^38^.

The smoking cessation intervention will be given in the outpatient department, by the surgeon, the nurses, or both. In discussions with smokers, the aim is to share information, persuade, motivate, and offer skills training and social support to quit smoking. The intervention will be performed during an outpatient appointment when the patient is registered on the waiting list and also during the preoperative visit. After surgery, when the stitches will be removed, Hb-CO and U-Cot tests will be repeated to verify participants’ smoking status to verify successful smoking cessation. Participants will be followed up to 12 months after surgery. Participants will receive a phone call or letter at 3, 6, and 12 months after surgery, asking them if any problems or complications had occurred (Figure 1). The description and ICD codes of complications will be recorded in the study form.

### Data from operation and definition of complications

The Finnish register of healthcare-associated infections (HAI) includes information about the operations of all surgically treated patients, regardless of whether the patient has had a postoperative infection or not. For this study, information about the surgery and any postoperative infection will be obtained from that register. A complication will be defined as any event which causes additional medical or surgical treatment, an additional radiological or laboratory test, a prolonged stay in hospital or any additional visit to a healthcare unit, following the criteria used by Nåsell et al.^26^. Data on complications have been mainly collected and will be completed from participants’ personal health records during their perioperative stay in hospital. These data will be combined with all available personal health data during 12 months after surgery and the information received during follow-up phone calls at 3, 6, and 12 months after surgery (Figure 1).

### Primary and secondary outcomes

The primary outcome is any complication occurring within 12 months after surgery. The number and types of complications (for example rapidly occurring complications, repeat surgery, and infections, stratified by types of surgery) are considered as secondary outcomes. Subgroup analysis based on patient characteristics and comorbidities will be carried out. Successful smoking cessation is a feasibility outcome.

